## Abstract

**Background:**

Bone and joint infection in adults arises most commonly as a complication of joint replacement surgery, fracture fixation and diabetic foot infection. The associated morbidity can be devastating to patients and costs the National Health Service an estimated £20,000 to £40,000 per patient.

Current standard of care in most UK centres includes a prolonged course (4–6 weeks) of intravenous antibiotics supported, if available, by an outpatient parenteral antibiotic therapy service. Intravenous therapy carries with it substantial risks and inconvenience to patients, and the antibiotic-related costs are approximately ten times that of oral therapy. Despite this, there is no evidence to suggest that oral therapy results in inferior outcomes.

We hypothesise that, by selecting oral agents with high bioavailability, good tissue penetration and activity against the known or likely pathogens, key outcomes in patients managed primarily with oral therapy are non-inferior to those in patients treated by intravenous therapy.

**Methods:**

The OVIVA trial is a parallel group, randomised (1:1), un-blinded, non-inferiority trial conducted in thirty hospitals across the UK. Eligible participants are adults (>18 years) with a clinical syndrome consistent with a bone, joint or metalware-associated infection who have received ≤7 days of intravenous antibiotic therapy from the date of definitive surgery (or the start of planned curative therapy in patients treated without surgical intervention). Participants are randomised to receive either oral or intravenous antibiotics, selected by a specialist infection physician, for the first 6 weeks of therapy. The primary outcome measure is definite treatment failure within one year of randomisation, as assessed by a blinded endpoint committee, according to pre-defined microbiological, histological and clinical criteria. Enrolling 1,050 subjects will provide 90 % power to demonstrate non-inferiority, defined as less than 7.5 % absolute increase in treatment failure rate in patients randomised to oral therapy as compared to intravenous therapy (one-sided alpha of 0.05).

**Discussion:**

If our results demonstrate non-inferiority of orally administered antibiotic therapy, this trial is likely to facilitate a dramatically improved patient experience and alleviate a substantial financial burden on healthcare services.

**Trial registration:**

ISRCTN91566927 - 14/02/2013

**Electronic supplementary material:**

The online version of this article (doi:10.1186/s13063-015-1098-y) contains supplementary material, which is available to authorized users.

## Background

Infections involving bone and joint have become increasingly common. In the National Health Service (NHS) in the UK, approximately 250,000 orthopaedic operations are performed annually including 160,000 hip and knee replacements [1]. Around 1 % of these are reported to be complicated by post-operative infection [2]. In addition, there are around 5,000 diabetic foot infections with associated osteomyelitis and a smaller number of infections of the axial skeleton. Treatment costs for bone and joint infections are estimated to be between £20,000 and £40,000 per patient [3–5].

Many consider a prolonged course (4–6 weeks) of intravenous (IV) antibiotics the “gold standard” treatment for bone and joint infections [6–8]. However, such practice derives from an era, prior to properly embedded pharmacokinetic principles, during which a widely held misconception that IV therapy is “stronger than oral therapy” was established. As a result, IV antibiotic therapy is often preferred to oral therapy and has become an accepted standard of care even for many non-acute infections. There is very limited evidence to support this practice. On the contrary, there is a growing body of literature, from both pharmacokinetic studies and from clinical outcome studies, to suggest that a wide range of infectious diseases (for example, pneumonia [9], urinary tract infections [10], low-risk neutropenic sepsis [11], skin and soft tissue infections [12] and endocarditis caused by *Staphylococcus aureus* [13]) can be effectively treated with oral therapy in the post-acute setting. Provided that agents are carefully chosen with respect to bioavailability and tissue penetration, there is no biologically plausible reason to believe that bone and joint infections should be any different.

A Cochrane review of five small trials involving a total of 180 participants with bone or joint infection showed no benefit of IV as compared to PO therapy [14], although the authors conclude that there is currently insufficient evidence to inform a widespread change in practice. Larger observational studies have reported high success rates for prosthetic joint infection with a shortened course of IV antibiotics or use of antibiotic cement spacers [15, 16], but observational comparisons are prone to confounding by indication.

Prolonged IV antibiotic therapy mandates placement of an intravenous vascular access device, which carries a risk of complications such as catheter-related infection and thromboembolic disease. Oral antibiotic therapy mitigates such risks [17, 18], is more convenient for the patient and is less costly. On the other hand, oral therapy carries a greater risk of poor adherence, gastrointestinal intolerance and variable serum levels related to drug bioavailability. Although clinicians can usually identify an appropriate oral antibiotic regimen with high oral bioavailability and good tissue penetration, this strategy has not yet been compared to intravenous treatment in a large clinical trial.

We conducted a single centre pilot study that concluded in March 2013 (Randomised open label study of oral versus intravenous antibiotic treatment for bone and joint infections requiring prolonged antibiotic treatment: Preliminary study in a single centre, NCT 00974493, Eudract Number: 2009-015744-42). The results were reviewed by an independent data monitoring committee (DMC), which advised that it was safe and appropriate to extend the trial. Thereafter, the trial switched to multicentre recruitment, and we transferred the data from the 228 participants in the pilot study to the multicentre trial database.

## Methods

### Study hypothesis and objectives

We hypothesise that per oral (PO) antibiotic therapy is non-inferior to IV antibiotic therapy in the treatment of bone and joint infection, as judged by the proportion of patients experiencing definite treatment failure during one year of follow-up. Our secondary objectives include: assessment of safety and tolerability (including serious adverse events, all-cause mortality, line complications, *Clostridium difficile* infection, early termination of allocated strategy); adherence to the PO antibiotics; a health economic analysis; patient reported outcome measures (PROMs) (Oxford Hip Score [OHS] and Oxford Knee Score [OKS] when appropriate, and EQ-5D-3 L); and possible or probable treatment failure as composites with definitive treatment failure.

The trial is in full compliance with the Helsinki Declaration and has ethical approval (REC reference 09/H0604/109 for the single centre preliminary study and REC reference 13/SC/0016 for the multicentre trial) from the NHS Health Research Authority.

### Trial participants

Participants are recruited from 30 secondary care centres, all of which are NHS hospitals in England or Scotland. All sites currently use 6 weeks of IV antibiotic therapy as their standard initial treatment for some or all categories of bone and joint infection, and all are able to deliver IV antibiotics to patients after discharge from hospital.

Participants are considered for inclusion when an infection specialist reviews a patient with a bone or joint infection. The contact is triggered by routine care pathway, for example, following referral by a surgical team, a referral from primary care direct to infectious disease services, or by following up a laboratory result. Informed consent is obtained from each participant by good clinical practice (GCP) trained research staff after assessing their understanding of the Patient Information Sheet (PIS) [see Additional files 1 and 2]. Eligibility is determined by the inclusion and exclusion criteria listed below.

### Inclusion criteria

The participant may be enrolled only if he or she meets *each* of the following criteria:Has a clinical syndrome comprising any of the following: a) localised pain or b) localised erythema or c) temperature >38.0 °C or d) a discharging sinus or woundIs willing and able to give informed consentIs aged 18 years or aboveHas received 7 days or less of intravenous therapy after an appropriate surgical intervention to treat bone or joint infection (regardless of pre-surgical antibiotics) or, if no surgical intervention is required, the patient has received 7 days or less of intravenous therapy after the start of treatment for the relevant clinical episodeHas a life expectancy > 1 yearHas a bone and joint infection in one of the following categories: a) native osteomyelitis (bone infection without metalwork) including haematogenous or contiguous osteomyelitis; b) native joint sepsis treated by excision arthroplasty; c) prosthetic joint infection treated by debridement and retention, by one stage revision or by excision of the prosthetic joint (with or without planned re-implantation); d) orthopaedic device or bone-graft infection treated by debridement and retention or by debridement and removal; e) spinal infection, including discitis, osteomyelitis or epidural abscess.

### Exclusion criteria

The participant may not enter the study if he or she has *any* one of the following:*Staphylococcus aureus* bacteraemia on presentation or within the last 1 monthBacterial endocarditis, either on presentation or within the last month (NB: there are no study mandated investigations, so participants are not required to have echocardiograms, blood cultures, or any other investigations to exclude endocarditis in the absence of a clinical indication)Any other concomitant infection which, in the opinion of the clinician responsible for the patient, requires a prolonged course of intravenous antibiotic therapy (for example, mediastinal infection or central nervous system infection)Mild osteomyelitis, defined as bone infection which, in the opinion of the clinical investigator, would not usually require a 6-week course of intravenous antibiotic therapyAn infection for which there are no suitable antibiotic choices to permit randomisation between the two arms of the trial (for example, where organisms are only sensitive to intravenous antibiotics)Previous enrolment in the trialSeptic shock or systemic features requiring intravenous antibiotic therapy in the opinion of the treating clinician (the patient may be re-evaluated if these features resolve)Evidence of being unlikely to comply with trial requirements following randomisation in the opinion of the investigatorClinical, histological or microbiological evidence of mycobacterial, fungal, parasitic or viral aetiology of the infectionReceiving an investigational medical product as part of another clinical trial

The use of antibiotic-loaded cement in spacers, bone substitutes or beads at the site of infection is not an exclusion criterion, but is recorded at baseline. Pregnancy, renal failure and liver failure are not exclusion criteria, provided suitable antibiotic options can be identified for both IV and PO therapy prior to randomisation.

### Randomisation

An electronic randomisation service, with telephone backup if necessary, is provided through a clinical trials unit. After confirming the patient’s eligibility, the randomisation service assigns a sequentially allocated study number and informs the investigator of the treatment allocation in real time and by confirmatory e-mail. Randomisation is stratified by site, to take account of variation in clinical practice among centres.

The local clinician or study nurse is responsible for documenting the participant’s enrolment in their clinical notes and for informing the participant’s general practitioner.

### Minimising bias

Blinding is not possible, since we consider that giving prolonged intravenous placebo would pose an unnecessary risk to participants and therefore would be unethical. Because an open label study is at risk of bias, we have appointed an endpoint review committee to review the clinical notes relating to any patient who fulfils the criteria for a potential treatment failure. All notes reviewed are redacted for personal identifiable data and for any information that might indicate the choice and route of antibiotic therapy. The endpoint review committee is therefore blind to treatment allocation. The notes are examined against objective criteria for meeting the primary endpoint.

### Study interventions: PO versus IV antibiotic strategy

The selection of individual antibiotic agents within the allocated strategy (that is, PO or IV antibiotics) is the responsibility of the infection specialist caring for the patient; the choice depends on microbiological assessment, the side effect profile and patient preference. In the event of a culture-negative bone or joint infection (or where there is a delay in availability of culture results), the infection specialist selects the most appropriate empiric therapy. If new information becomes available, the infection specialist may change the choice of antibiotic agent but should remain within the allocated route of administration strategy; if this is not possible, the participant will have reached an endpoint.

If randomised to IV strategy, participants are expected to complete 6 weeks of IV antibiotic therapy. Where it is common practice to use adjunctive oral agents in patients treated with IV therapy (for example, oral rifampicin as adjunctive therapy for biofilm-related staphylococcal infection), such therapy will be allowed.

If randomised to the PO strategy, participants are expected to commence PO therapy within seven days of definitive surgical management (or, if managed without surgery, from the start of antibiotic therapy for that clinical episode). If a participant allocated to the PO strategy requires IV antibiotic therapy for an unrelated intercurrent illness during the initial 6 weeks of treatment, or experiences vomiting or inability to swallow, or concerns arise about absorption of oral medication, then IV antibiotic therapy may be substituted for up to five days. If IV antibiotic prescribing exceeds five days, the patient will have met a secondary endpoint, but will still contribute to the intention-to-treat analysis.

Follow-on antibiotic treatment after the initial 6 weeks may be prescribed in either arm of the trial, but the choice of agent, duration and route of administration are not governed by the trial protocol.

If continuing in the randomised strategy (IV or PO) is no longer compatible with optimal clinical care, the clinician must commence appropriate alternative therapy. Appropriate reasons for discontinuing the allocated treatment might include lack of suitable medication within the allocated strategy, adverse reactions, contraindications or susceptibility testing results. Failure to maintain intravenous access is an appropriate reason for discontinuing IV antibiotics. A wound discharge or other clinical signs related to the incident infection, or its apparent resolution, are not appropriate indications for changing from one treatment strategy to the other, since there is equipoise regarding efficacy.

There are no formal withdrawal criteria in this study other than at the request of a participant. All patients are free to withdraw their consent at any time; if they elect to withdraw from the allocated treatment strategy during the randomised treatment phase, they will meet a secondary endpoint but may still be followed up and be included in the analysis provided that appropriate consent is given.

Any medical decision to withdraw a participant from the randomised strategy is discussed with the chief investigator (CI) or the trial physician. Changing the antibiotic whilst remaining within the allocated strategy need not be discussed, but a clinician with appropriate training in managing infection must make such a decision.

The infection specialist may adjust dosage based on renal or hepatic function, drug interactions or other factors according to drug labelling information, the British National Formulary and local pharmacy guidelines. All antibiotics used (including dosage, route of administration and duration) are recorded from the day of randomisation through to final follow-up at one year (Fig. 1).

**Fig. 1 Fig1:**
[figure not shown]
Participant pathway for the OVIVA trial

### Assessments

When a participant is an inpatient, the study clinician or research nurses will maintain contact with the clinical team to identify potential endpoints, and to ensure implementation of the randomised antibiotic strategy. Following hospital discharge, participants are seen according to clinically determined follow-up plans. Trial-specific data are obtained from the case record at 6 weeks (range from day 21 to day 63), 4 months (range day 70 to day 180) and 1 year (range day 250 to day 420). If the patient does not attend clinic within the specified date ranges, the investigator arranges a telephone review with the participant or the participant’s general practitioner (GP) to identify potential endpoints or serious adverse events. If, based on the telephone discussion, clinical review is indicated, the investigator organises this and advises the patient accordingly.

A study clinician reviews the source documents from routine care visits when completing investigator reviews. They record:Microbiology and histology results and date of discharge (first review only)Outpatient visits since randomisationSerious adverse eventsRe-admissions for inpatient careType of intravenous catheter (line) used and any line-related complicationsEpisodes of *Clostridium difficile* associated diarrhoeaAntibiotic use to date (including dosage, route and model of care, for example, district nurse, self-administered or daily clinic visits)Presence or absence of any potential endpointsReasons for not completing the planned antibiotic course (if applicable).

### Outcome measures

Endpoints are identified by prospective surveillance throughout the year post-randomisation.

The primary endpoint is definite failure of infection treatment, where definite failure is indicated by one or more of the following:Isolating bacteria from two or more samples of bone/spine/peri-prosthetic tissue, where the bacteria are phenotypically indistinguishableIsolating a pathogenic organism (for example, *Staphylococcus aureus,* but not *Staphylococcus epidermidis*) on a single, closed biopsy of native bone or spineDiagnostic histologic findings on bone or peri-prosthetic tissueFormation of a draining sinus tract arising from bone or prosthesisRecurrence of frank pus adjacent to bone or prosthesis.

Secondary endpoints are:Serious adverse events (SAEs), including death (that is, all-cause mortality)IV line complications (infection, thrombosis or other events requiring early removal or replacement of the line)“Probable” or “possible” treatment failure, as composites with definite treatment failure. These are determined by blinded endpoint committee review and defined by the presence of any one of the following criteria:Loosening of a prosthesis, confirmed radiologicallyNon-union of a fracture after 6 months, confirmed radiologicallySuperficial spreading erythema, treated as cellulitis with an antibiotic for >1 week; where results from deep tissue samples do not meet the primary endpoint as described above

Where appropriate deep tissue samples have been sent for microbiology and results of the culture are negative, and any of a), b) or c) are met, then the endpoint will be regarded as “possible”. On the other hand, where deep tissue samples are not sent for microbiology, and any of a), b) or c) are met, then the endpoint will be regarded as “probable”4.Early termination of the planned 6-week period of oral or IV antibiotic therapy because of adverse events, patient preference or any other reason5.Resource allocation determined by: a) length of inpatient hospital stay; b) frequency of outpatient visits; or c) antibiotic prescribing costs6.Quality of life evaluated by EQ-5D-3 L questionnaire7.Oxford Hip and Knee Scores (where infection is in the hip or knee)8.Adherence to oral medication.

The study clinicians determine secondary endpoints 1, 2, 4 and 5. The blinded endpoint review committee determines primary endpoints and secondary endpoint 3, by using redacted notes. Participant questionnaires determine secondary endpoints 6 and 7. Secondary endpoint 8 is determined by questionnaire in all centres, and by medication event monitoring systems (MEMS) at four sentinel sites.

### Endpoint review committee

The endpoint review committee (ERC) is composed of three independent clinicians (two infectious disease specialists and one orthopaedic surgeon) with expertise in the management of orthopaedic infections.

The hospital notes relating to the potential endpoint are redacted for both personal identifiable information and specifics of antibiotic treatment or IV line insertion, which could indicate the route of administration of antibiotics. The redacted notes are forwarded to the ERC, who determine whether an endpoint has been met, either by consensus or by a vote called by the chair if consensus cannot be reached.

The ERC is only required to review definite or potential treatment failures. All other endpoints are determined directly by the local study clinicians.

### Adherence and medication event monitoring systems (MEMS)

Patient adherence to antibiotic therapy may directly influence the outcome of treatment. All participants randomised to the oral strategy therefore receive questionnaires to monitor adherence. A subgroup of participants randomised to the intravenous strategy and taught to self-administer also receive adherence questionnaires. In order to avoid intrusion and to minimise undue influence on patient behaviour, participants do not receive any direct antibiotic adherence support (such as text message reminders or telephone monitoring), but the importance of adherence is explained at the time of recruitment and reinforced at the time of discharge. The Patient Information Sheet (PIS) includes information written by the patient representatives which explains the importance of, and rationale behind, medication adherence.

In order to validate the adherence questionnaire returns, selected sites (Oxford University Hospitals, Guy’s and St. Thomas’ Hospitals, The Royal National Orthopaedic Hospital and The Royal Free Hospital, London) dispense oral antibiotics in pill containers with MEMS. This method of monitoring has become standard in studies of medication where adherence is critical [19, 20]. Sensors in the caps detect opening and closing, and record these events with a date stamp. The sensors are read at a later date to verify whether patients opened and closed their bottles at times that are consistent with their prescription. MEMS are used only with specific consent from participants. If more than one antibiotic is prescribed, we use the MEMS sensors on the more frequently dosed antibiotic. If changes to antibiotic prescriptions are required after discharge, trial participants continue with only paper adherence questionnaires.

### Safety

Since the OVIVA trial does not involve randomisation to a specific therapy, it is not a “Clinical Trial of an Investigational Medicinal Product,” as defined by the European Union (EU) directive 2001/20/EC. Safety reporting therefore refers to the trial sponsor and the DMC. We record all SAEs identified within a year of randomisation. We consider episodes of definite or potential treatment failure as SAEs.

If an investigator becomes aware of an unexpected SAE during the trial, he or she contacts the CI, who clarifies clinical details and reports the SAE to the sponsor. If, in the opinion of the CI or the sponsor, an unexpected SAE may be relevant to participant safety, a detailed report including an assessment of causality and severity is forwarded to the DMC, which in turn makes a recommendation regarding the safety of the trial in the light of this report.

Expected SAEs that do not undergo expedited reporting are defined as:Complications of bone/joint surgeryComplications of the bone/joint infection for which the patient is undergoing treatment (including potential endpoints)Drug reactions as detailed in the product literature (that is, the summary of product characteristics (SMPC) or British National Formulary)Drug reactions for concurrent medications given for routine clinical care as detailed in the product literature (the SMPC or British National Formulary)Intercurrent illness causally related to the comorbid conditions that the investigator believes are likely diagnoses, given the patient’s history, age and other factors.

The investigators use their judgement, such that SAEs technically meeting definitions above for expectedness, but that seem unexpected in terms of severity, duration or other factors, may be reported as unexpected.

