#### Secondary endpoints

Secondary analyses will include: (i) a per-protocol analysis based on all participants who have received at least 4 weeks of randomised therapy and (ii) intention-to-treat and per-protocol analyses in the subgroup with “definite” or “definite”/“probable” infection at randomisation. These secondary analyses will focus on consistency of point estimates and 95 % CI, rather than formal comparison with the 7.5 % non-inferiority margin. We will similarly compare the proportions of participants with secondary endpoints, or the distributions of continuous secondary outcomes (rank sum tests). Subgroup analyses will use interaction tests to determine the consistency of treatment effects by type of infection and infecting pathogen. We record treatment intentions for both intravenous and oral routes at baseline before randomisation. Subgroup analysis will compare efficacy of intravenous versus oral antibiotic therapy according to whether or not rifampicin was used as an adjunctive therapy in the intravenous and oral arms (four subgroups). We will also conduct subgroup analyses according to the clinician’s specific antibiotic intentions, as recorded prior to randomisation.

A survival analysis will be performed to assess post-randomisation surveillance bias, which would present as a delay in time to meeting an endpoint in one randomised group. Other secondary analyses will include regression models (logistic (binary) or quantile (continuous)) to calculate estimates of treatment differences for the primary and secondary endpoints adjusted for age, comorbidity, infecting pathogen and type of surgical intervention.

The statistical analysis plan will be locked prior to analyses being undertaken and will be made freely available at the time of publication.

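### Treatment failures are counted as SAEs, so the between-arm SAE comparison partly re-counts the efficacy outcome

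*Protocol article*

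**What the plan says.** The Safety section of the protocol article gives the rule: "We consider episodes of definite or potential treatment failure as SAEs". The collection window is the same year as for the primary endpoint: "We record all SAEs identified within a year of randomisation". The same section lists potential endpoints among expected SAEs. That exempts them from expedited reporting, but they remain SAEs.

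Under Outcome measures, the first secondary endpoint is "Serious adverse events (SAEs), including death (that is, all-cause mortality"). The objectives place it under "assessment of safety and tolerability (including serious adverse events, all-cause mortality, line complications" and related items. On who decides, the article says "The study clinicians determine secondary endpoints 1, 2, 4 and 5", whereas "The blinded endpoint review committee determines primary endpoints and secondary endpoint 3, by using redacted notes". Treatment is open-label: "Blinding is not possible, since we consider that giving prolonged intravenous placebo would pose an unnecessary risk".

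The analysis text under Secondary endpoints says "We will similarly compare the proportions of participants with secondary endpoints". It does not separate failures from other SAEs.

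**The concern.** Read together, these statements make one event count twice: once as efficacy failure and once as a safety event. A reader who takes endpoint 1 as a measure of harm from the treatment route would be reading a mixture of treatment harm and treatment failure.

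Two things follow. First, the size and even the sign of the SAE difference depend on what happens to failure, so the SAE proportion can misstate the difference in other serious events. Second, the rule covers potential failures as well as definite ones. A potential failure is first flagged by a clinician who knows the allocation, and the article does not make its SAE status depend on the ERC's decision. The Discussion accepts that the open-label design is open to bias, most likely in favour of IV. If oral patients were flagged more readily, the ERC would filter the excess out of the primary endpoint, but endpoint 1 would keep it.

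At stake is the interpretation of a named safety endpoint, chiefly for serious drug reactions and other serious events that have no endpoint of their own. The primary conclusion is not affected.

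**Working it through.** **Inputs from the article.** The planned total is 1,050, randomised 1:1, with 10% loss to follow-up (Sample size). This leaves 1,050 × 0.90 / 2 = 472.5, taken as 472 per arm. The pooled failure rate is 12.5% (Sample size; the Discussion identifies it as the primary endpoint rate, hence definite failure only). The margin is 7.5 points.

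**Check on the plan's own figure.** A one-sided 5% two-proportion calculation of 5% against 10% with 90% power gives 474 per arm, or 948 in total. Allowing for 10% loss gives 1,054 (948 / 0.9) or 1,043 (948 × 1.1), so 1,050 is reproduced. The article gives no figure for SAEs.

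**Assumptions.** The article states no SAE rates. Non-failure SAE rates *s* are therefore varied, always 5 points higher on IV, and are taken as independent of failure *f*.

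**Formulas.** Any-SAE risk = 1 − (1 − *f*)(1 − *s*). Power (two-sided 5%) = Φ(difference / SE − 1.96), with SE = √{[p₁(1 − p₁) + p₂(1 − p₂)] / 472}.

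**Worked case, *s* = 15% IV and 10% oral.**
- Failures excluded: difference 0.050; SE = √[(0.1275 + 0.0900)/472] = 0.0215; power = Φ(2.33 − 1.96) = 64%.
- Failure 12.5% in both arms: IV 1 − 0.875 × 0.85 = 25.6%; oral 1 − 0.875 × 0.90 = 21.3%; difference 4.4 points; SE 0.0275; power = Φ(1.59 − 1.96) = about 36%.
- Failure 10% IV and 15% oral (mean 12.5%; the 5-point excess is inside the margin): IV 1 − 0.90 × 0.85 = 23.5%; oral 1 − 0.85 × 0.90 = 23.5%; difference 0.
- Failure 15% IV and 10% oral: IV 1 − 0.85 × 0.85 = 27.75%; oral 1 − 0.90 × 0.90 = 19.0%; difference 8.75 points; power 89%.

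**Range (IV minus oral difference in points, with power).**

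| Non-failure SAEs, IV v oral | Failures excluded | Failure 12.5% both | Failure 10% IV, 15% oral | Failure 15% IV, 10% oral |
|---|---|---|---|---|
| 10% v 5% | 5.0; 83% | 4.4; 40% | −0.25; 3% | 9.0; 94% |
| 15% v 10% | 5.0; 64% | 4.4; 36% | 0.0; 3% | 8.75; 89% |
| 20% v 15% | 5.0; 53% | 4.4; 32% | 0.25; 3% | 8.5; 83% |
| 25% v 20% | 5.0; 45% | 4.4; 30% | 0.5; 4% | 8.25; 78% |

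**Extent of overlap.** The share of participants with any SAE who have a failure is 0.125 / any-SAE risk. This is 0.125/0.2125 = 59%, 0.125/0.256 = 49% and 0.125/0.344 = 36% for non-failure rates of 10%, 15% and 25%.

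The 12.5% covers definite failure only, whereas the rule also takes in potential failures, so the overlap is probably larger. With equal rates in both arms the difference is 5 × (1 − *f*): 4.0 points if 20% of patients are flagged and 3.75 points if 25% are. Those two rates are assumptions.

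**The case against.** The strongest reply is that the sentence is a reporting rule. It sits in a section on recording SAEs and routing them to the sponsor and data monitoring committee, and failure in these patients is a serious event. How SAEs are tabulated is commonly left to the analysis plan, which is not shown here and may separate failures. That stands in part: recording failures as SAEs is sound and should continue. But the article goes beyond recording. It fixes what an SAE is, makes SAEs an endpoint and says proportions will be compared, so the overlap follows from stated text and not from a missing detail.

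A reader might infer that the overlap hides the safety difference between routes. The article does not support this. Line complications (endpoint 2) and early termination (endpoint 4) are separate endpoints. All-cause mortality and *C. difficile* are named separately in the objectives, although *C. difficile* is not in the endpoint list. Those harms stay visible whatever happens to the pooled proportion. Nor is the effect only one of masking, since it can also exaggerate a difference.

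A reader might also infer that the rule undoes the blinded committee's protection. It does not. That protection covers the primary endpoint and secondary endpoint 3, and both are untouched. Potential failures are sent to the committee; the narrower point is that SAE status does not depend on its ruling. The article does not say outright what becomes of a rejected case in the SAE analysis.

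Finally, removing every clinician-flagged potential failure would let unblinded flags take events out of the safety comparison. This objection is correct and shapes the fix.

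**Conclusion.** The point holds for the pooled SAE endpoint only. As written, endpoint 1 partly re-counts efficacy failure, including unblinded flags of potential failure. For an assumed 5-point difference in non-failure SAEs, equal failure of 12.5% trims the difference only to 4.4 points. The loss of power is larger: from between 45% and 83% to between 30% and 40%. A 5-point failure difference in the opposite direction brings the SAE difference to within half a point of zero; one in the same direction raises it to between 8.25 and 9.0 points.

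These sizes rest on assumed SAE rates and on independence of failure from other SAEs. The article claims no power for SAEs, so the power figures only illustrate lost information. The direction of the distortion depends on the failure results and cannot be known in advance. The point is worth correcting because the endpoint cannot be read as a measure of non-failure harm, but it does not threaten the primary analysis.

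**What to change.** Keep recording definite and potential failures as SAEs for safety oversight. For secondary endpoint 1, define the main between-arm comparison as participants with at least one SAE other than an ERC-adjudicated failure of the index infection (definite, probable or possible). Count a potential failure that the ERC rejects only if the event meets SAE criteria in its own right. Alongside, show the comparison for all SAEs and a sensitivity version that excludes every event referred to the ERC.

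The cost is a short addition to the endpoint definition and one extra table, from data already collected. The drawback is that the safety count then depends on ERC classification; the two accompanying versions show how much that matters.
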